### Alcohol Availability & Harm

Systematic reviews, and reviews of reviews, have concluded that legislative measures, including control of the ease with which alcohol can be obtained, can be effective in reducing alcohol-related harms [15–17]. These ‘availability’ interventions include limits on the age at which alcohol may be purchased, as well as controls on the number and proximity of outlets selling alcohol (physical availability) and their hours of sale (temporal availability). There is consistent evidence suggesting an association between increased physical and temporal availability of alcohol and higher rates of consumption and associated alcohol-related harms [18–23], including several UK studies [24–27].

Two recent studies found that local authorities in England with a more intensive alcohol premises licensing regime experienced an additional 5% reduction in alcohol related hospital admissions rates from 2009 to 2015 (or 2% annually) [28] as well as an additional 4–6% reduction in public nuisance and alcohol-related crime rates [29], compared with what would have been expected had these local areas had no active licensing policy in place [30]. The density of alcohol outlets has been shown to be higher in deprived areas in both England and Scotland [25, 31]. Whilst the direction of causation for this relationship is unknown, it raises the possibility that alcohol premises licensing policy could have a greater positive impact on health harms in these areas, and even reduce alcohol-related health inequalities [25, 32].

The extent to which increased availability causes alcohol harms, and if so, the mechanisms by which effects are exerted remains unclear, since much of the research is cross-sectional and the validity of measures of the availability of alcohol premises is variable [21, 33–37]. A recent review of 160 studies found that a causal relationship between public health activities, specific local licensing controls, indicators and types of availability and alcohol-related harms is not clear or consistently demonstrated in the literature [33]. The same study noted the difficulty of translating the research into practice, due both to these limitations and the lack of clear theories of change [33]. Examining the relationship between these three sets of variables – public health team activity, the licensing regime, and local level health/crime outcomes – is the core focus of this study.

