#### Control areas

In England, there are 326 lower-tier local authority areas in total and potential control areas will be identified using genetic matching. In a natural experiment such as this, it is not feasible to randomise PHTs to active or inactive groups, but it is important to address potential bias that may have been introduced by pre-existing differences between intervention and control areas. Genetic matching uses algorithms to select control areas to ensure that intervention and control areas are as similar as possible on predetermined covariates (Table 2). It seeks to minimise the Generalised Mahalanobis Distance (GMD), which is here a weighted multivariable indicator of the difference between intervention and control areas across all chosen covariates.

We will use genetic matching to identify 14 control areas for the 14 English intervention areas. Following matching, we will attempt to recruit the control areas with the most similar distributions of matching variables to the intervention areas. If an identified control area declines to participate, or is unsuitable due to high activity levels, we will exclude this area and re-run the matching with the remaining potential control areas.

Due to the much restricted pool of potential control areas in Scotland, compared to England, the same matching method could not be used. Instead, the values of every covariate outlined in Table 2 were normalised across all local authorities such that the highest value corresponded to 100 and the lowest to 0. For each of the 6 selected case areas, the cumulative root mean square error across all covariates was calculated for every potential control. The final set of control areas was identified by selecting the pool of controls which minimised the cumulative error across all 6 case-control pairs. Where a potential control area from this pool declines to participate in the study or is found to be a high activity area, we will select the next best alternative using the same cumulative error-minimisation approach.

**Table 2 Tab2:** Selected covariates for genetic matching

Variable category	Country	
	England	Scotland
Deprivation/inequality	-Percentage of population living in a rural area	-Percentage of population living in a rural area

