	-Percentage of population living in area in most deprived quintile -Long-term unemployment (jobseekers claimant > 12 months)	-Scottish index of Multiple Deprivation score (average score across data zones for each local authority)
Population/outlet density	-Population density per square kilometre	-Estimated mid-year population -Population density per square kilometre -On-licence density -Off-licence density
	-On-licence density	
	-Off-licence density	
Alcohol-related harm	-Alcohol-related hospital admissions (standardised rate; narrow measure) -Alcohol-related violent crime	-Alcohol-related hospital admissions (standardised rate)
Demographic variables	-Median age	-Median age

Potential variables for inclusion in the matching processes were identified using a modified Delphi approach [67]. Matching variable selection was refined following an evaluation of covariate balance from initial propensity score matching analyses (presented at ExILEnS team meeting 22.09.17), and discussion with members of the ExILEnS team ([name], [name], [name] and [name]). All of the covariates included in the matching process were measured at baseline (2009–2011).

Table 2 lists the final covariate set which will be used for matching for English and Scottish local authority areas. The covariate list differed between the two countries due to differences in the publicly available data at local authority level.

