### Power calculations

No quantitative data is available on the effect of public health engagement in licensing on alcohol-related harms. The assumed mechanism by which such engagement might reduce harms however, is by influencing the local licensing system. Statistical power estimations therefore have been based on effect sizes from two recent studies of the effect of alcohol premises licensing on alcohol-related hospital admissions and reported crime rates at the level of ‘lower tier local authority’ (LTLA) in England [28, 29]. Areas with active alcohol licensing policies had an average additional 2% (95% CI -3%:-2%) annual reduction in alcohol-related hospital admissions in the period up to and including 2013 compared to those without such policies [28]. Similarly, for the period up to 2013, an additional 4–6% annual decrease was seen in alcohol-related violent crimes, sexual crimes and public order offences in areas with active licensing policies compared to those with none [29].

We used the methodology developed by Edland for power calculations of linear mixed effects models with random slope [68]. Based on the previous studies, we conducted separate sample size calculations for alcohol-related hospital admissions and reported crime rates. For both analyses we assumed a standard level of statistical significance α (5%) and statistical power β (80%), and further assumed a 9-year follow-up (2009–2018) and a two-sided alternative. Table 4 outlines the detectable effect size with 20 intervention and 20 control areas.

**Table 4 Tab4:** Sample size data

	Expected average effect size %/year (slope)	Between-slope variance	Residual variance model	Number of areas in each group
*From previous study of impact of licensing on alcohol-related crime* [29]				
Crime rates^a^	−4.00% (−0.04)	0.003	0.03	29
	−5.00% (−0.04)	0.003	0.03	19
	−6.00% (−0.06)	0.003	0.03	13
*From previous study of impact of licensing on alcohol-related hospital admissions* [28]				
Rates	−2.31% (−0.229)	0.110	0.011	34
*Current study - minimum detectable effect size with proposed sample size*				
20 areas per group	−3.00% (−0.296)	0.110	0.011	20

^a^Effect size is a range between 4 and 6% as estimated by d Vocht et al. (2016) using quadratic trends

Based on Table 4, we expect the study to be able to detect effects on our outcomes within the range found in previous observational studies with 20 intervention and 20 control areas.

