The first draft of each measure will define dimensions and indicators for different categories of PHT or licensing activity and will be developed based on current research literature and published best practice guidance. This draft will be used to code data a subset of interventions areas, and then all intervention areas, revising as needed at each stage. The resulting measure will be sent to UK-based public health and licensing experts, to review for clarity, completeness and relevance and then further revised based on their feedback. The range of practice for each included indicator of intensity will be analysed by each researcher, and discussed and combined to develop a single measure and defined grading scales for each included indicator. This version will then be applied independently by two researchers to a subset of intervention and control area data, and the resulting scores compared in discussion, checking for consistency and face validity. The final stage of development will involve deciding, using our data, and in consultation with experts, whether and how different dimensions or indicators within the measure should be weighted. Weightings will also be informed by parallel work by the team to further develop a theory of change for PHT involvement in licensing.

Once the measures have been finalised using this iterative process, they will be reapplied to the data for all intervention and control areas to calculate intensity scores for each 6 month period April 2012 to March 2019. Two researchers will apply the measure to 10% of areas (*n* = 4) to examine inter-rater reliability. Where identified, discrepancies will be discussed and assessed by a third reviewer as needed. The scoring system will then be revised and another 4 areas assessed by two reviewers. In the event of further serious discrepancies, this process will be repeated. We will report the inter-rater reliability of the finalised measure.

The agreed intensity scores will be used to examine the relationship between intervention intensity, licensing regime activity and alcohol-harm outcomes.

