### Analysis of primary outcomes

We will evaluate temporal trends in all key outcomes from 2009 to 2018 and compare these in intervention and control areas using hierarchical log-rate growth models. This method was previously used by members of the research team to investigate the association between a metric of ‘licensing activity’ and alcohol related hospital admissions [28, 30] and crime rates [29] in England.

An additional feature of this study over and above those studies, is the chunking of the intervention intensity measure into 6-month intervals enabling specific exploration of causal effects through inclusion of pre/post indicators and interactions in the growth models as well as the use of ‘Differences-in-Differences’ statistical methods [77]. Inferences about causality can be made through quantitatively evaluating, using a pre-specified plan based on the emergent theory of change, whether there is statistical evidence of changes in longitudinal trends in outcome measures that coincide with the expected effect of the intervention (and is not present in the corresponding control area). Where data is available we will analyse outcomes by deprivation and gender.

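### The matching covariates omit the 2009–2011 licensing regime, so part of any effect of an already active licensing authority could be credited to public health engagement

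*Protocol article*

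**What the plan says.** The Control areas section gives the reason for matching: "it is important to address potential bias that may have been introduced by pre-existing differences between intervention and control areas". It then fixes the variables: "Table 2 lists the final covariate set which will be used for matching for English and Scottish local authority areas". All were measured in 2009–2011.

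- **England:** rurality, deprivation, long-term unemployment, population density, on- and off-licence density, alcohol-related admissions, alcohol-related violent crime and median age.
- **Scotland:** a similar set, with a deprivation score and mid-year population, and without crime.
- **Neither country:** whether a cumulative impact or overprovision policy was in force, how licence applications were decided, or any licensing-activity metric.

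The article reports that the missing variable is associated with the outcomes. Under Alcohol Availability & Harm: "local authorities in England with a more intensive alcohol premises licensing regime experienced an additional 5% reduction in alcohol related hospital admissions rates" (2009 to 2015). Under Power calculations: "Areas with active alcohol licensing policies had an average additional 2% (95% CI -3%:-2%) annual reduction in alcohol-related hospital admissions", and for crime "an additional 4–6% annual decrease was seen in alcohol-related violent crimes, sexual crimes and public order offences in areas with active licensing policies", both for periods up to 2013.

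Under Data collection, the finalised public health and licensing measures are applied to "calculate intensity scores for each 6 month period April 2012 to March 2019". The Analysis of primary outcomes section compares 2009–2018 trends between groups in hierarchical log-rate growth models, with pre/post indicators, interactions and difference-in-differences methods added.

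**The concern.** The primary question is about engagement by public health teams, not about the licensing authority's own strictness. A regime that was already active before 2012 is a potential confounder. The article's evidence links it to steeper falls in harm, and it may be related to where teams could become active. Three features of the article make that second link plausible:

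- Selection favours sustained high-intensity engagement from the earliest time point.
- Involvement in other licensing initiatives is one of the sources used for selection.
- The Background describes some Scottish areas adopting large overprovision policies while others resisted public health involvement.

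If the two go together, intervention areas would show falling harm for a reason that Table 2 does not balance. The effect assumed in the power section is itself the licensing effect, so such a bias would resemble the expected result.

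The scores from April 2012 onward cannot simply be used to adjust for this. The article's assumed mechanism is that engagement changes the licensing system, so those scores may lie on the causal path, and adjusting for them could remove part of the effect of interest.

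**Working it through.** **1. Reproduce the plan's figure.** Table 4, current-study row: slope −0.296 (−3.00% per year), between-slope variance 0.110, residual variance 0.011, two-sided 5%, 80% power. I assume 10 annual points, so the sum of squared time deviations is 82.5.

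n per group = 2 × (1.960 + 0.842)² × (0.110 + 0.011/82.5) / 0.296² = 19.7, against 20 stated. This reproduces.

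**2. Standard error of the slope difference at 20 per group.**

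- Admissions: √[2 × (0.110 + 0.011/82.5)/20] = 0.105. At 3.00/0.296 per cent per unit, this is about 1.06% per year.
- Crime: √[2 × (0.003 + 0.03/82.5)/20] = 0.0183.

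**3. Spurious slope when engagement has no effect.** Let d be the share of intervention areas with an active pre-2012 regime minus the share of control areas. The article does not give d, so I assume 0.2 to 0.5. The spurious difference is d × (licensing effect per year). Two admissions effects are used: 2.31% per year (Table 4), and the 5% reported for 2009–2015 spread over six years, 1 − 0.95^(1/6) = 0.85% per year.

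| d | Admissions at 2.31%/yr | Admissions at 0.85%/yr | Crime at 4–6%/yr |
|---|---|---|---|
| 0.2 | 0.46 | 0.17 | 0.8–1.2 |
| 0.3 | 0.69 | 0.26 | 1.2–1.8 |
| 0.5 | 1.16 | 0.43 | 2.0–3.0 |

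The licensing effects are English. If they apply only to the 14 English pairs of 20, multiply by 0.7. The admissions range becomes 0.32–0.81% per year at 2.31%, or 0.12–0.30% at 0.85%.

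**4. Chance of a significant result with no true effect.** Φ(−1.96 + b/SE) + Φ(−1.96 − b/SE), where b is the spurious slope on the scale of Table 4. This applies to a plain comparison of 2009–2018 slopes over all 20 pairs.

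| d | Admissions, 2.31%/yr | Admissions, 0.85%/yr | Crime, 4–6%/yr |
|---|---|---|---|
| 0.2 | 7% | 5% | 7–10% |
| 0.5 | 19% | 7% | 19–37% |

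**5. What the planned analysis removes.** Outcomes start in 2009 and intensity scores in April 2012, leaving about 13 quarters before and 27 after, to the end of 2018. If a regime adds a constant extra slope throughout, the pre-period shows it and a pre/post slope interaction nets it out. If the regime's effect grows or fades after 2012, that change appears as a change in slope at the time engagement begins, and the interaction does not remove it. Difference-in-differences on levels does not remove trends that were already diverging. Matching on the 2009–2011 level of harm does not balance slopes.

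**The case against.** The strongest reply is that the analysis already includes pre/post indicators, interactions and difference-in-differences, with outcome data from 2009. That stands for a stable regime effect and narrows the concern to an effect that changes over time, or a slope difference that the short pre-period measures poorly.

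Other replies also have force:

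- **Imbalance is not shown.** Nothing in the article says that areas with active teams had stricter authorities before 2012.
- **The licensing effect is not established as causal.** The figures are observational and English, and the article cites a review of 160 studies that found no clear or consistent causal link. It does not say how far the figures reflect regimes in force before 2012, and carrying them unchanged to 2018 is an assumption.
- **The covariates were chosen with care.** The article describes a modified Delphi process, a balance check and limits on public data. Outlet density and baseline harm are partial proxies.
- **The size is moderate.** Even 1.16% per year is well below the 3.00% minimum detectable effect.
- **The first half-year English score could be near-baseline.** The public health role dates from 2011 and licensing policies run for five years. This has some merit, but a 2009–2011 measure avoids the ambiguity.

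One reply rules out equal treatment of Scotland. Health boards there were made statutory consultees under the 2005 Act, and early public health involvement is linked to overprovision policies. A pre-2012 overprovision declaration may therefore result from engagement. An overprovision statement is also mandatory, so its mere presence would not distinguish areas.

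**Conclusion.** The point holds in limited form. The omission is a fixed choice stated in the article, and it leaves out a variable that the article's own evidence associates with the outcome trends. Under an assumed imbalance of 0.2 to 0.5, a plain comparison of 2009–2018 trends would carry a spurious admissions difference of about 0.5–1.2% per year at 2.31% per year, or 0.2–0.4% at 0.85%. These sizes rest on the assumed imbalance, on reading the cited associations as effects, on their persisting to 2018, and on their applying in both countries.

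A reader might infer that the comparison is known to be biased in favour of engagement, or that the planned analysis has no protection against this. The documents support neither. Imbalance is possible rather than demonstrated, and the slope interactions would remove a constant regime effect. Nor do the documents show that the existing matching must be redone.

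**What to change.** **England.** Record the 2009–2011 regime for each area: whether a cumulative impact policy was in force, or the team's existing licensing-activity metric if it covers those years. Report its balance by group. Enter it and its interaction with time in the growth models. Include it in any matching re-run made because a control declines or proves unsuitable.

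**Scotland.** Record whether any locality had been declared overprovided before 2012, and use this only in a sensitivity analysis.

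**Both.** Keep the licensing scores from April 2012 onward for mediation analysis, not for confounder adjustment.

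**Cost.** Some data extraction from licensing policy statements or the team's existing dataset, a small loss of precision with 40 areas, and slightly looser balance on the other covariates where matching is re-run.

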### Outcomes of interest

Longitudinal data on a set of key alcohol harm outcome indicators’ will be collected for each intervention and control area from 2009 to 2018 as shown in Table 3. Some alcohol-related harm takes time to develop so there will be some lag. Implementation of these lags will be specified prior to the analyses being undertaken by reference to relevant literature and in consultation with our advisory group.

**Table 3 Tab3:** Outcome Indicators & Data Sources

Outcome indicator	Source	
	England	Scotland
Quarterly alcohol-related hospital admissions	PHE	Information Services Division (ISD) Scotland
Quarterly alcohol-related and alcohol-specific mortality	PHE	National Records of Scotland (NRS)
Quarterly reported crime rates with significant attribution of alcohol abuse (violent, sexual, and public order offences)	Office for National Statistics (ONS)	Scottish Government
Weekly ambulance call outs for weekdays/weekends, both daytime and night-time	English Ambulance Services	Scottish Ambulance Service
Weekly A&E attendance rates for weekdays/weekends, both daytime and night-time	NHS Hospital Episode Statistics (HES) Data Access Request Service (DARS)	ISD Scotland

### Power calculations

No quantitative data is available on the effect of public health engagement in licensing on alcohol-related harms. The assumed mechanism by which such engagement might reduce harms however, is by influencing the local licensing system. Statistical power estimations therefore have been based on effect sizes from two recent studies of the effect of alcohol premises licensing on alcohol-related hospital admissions and reported crime rates at the level of ‘lower tier local authority’ (LTLA) in England [28, 29]. Areas with active alcohol licensing policies had an average additional 2% (95% CI -3%:-2%) annual reduction in alcohol-related hospital admissions in the period up to and including 2013 compared to those without such policies [28]. Similarly, for the period up to 2013, an additional 4–6% annual decrease was seen in alcohol-related violent crimes, sexual crimes and public order offences in areas with active licensing policies compared to those with none [29].

We used the methodology developed by Edland for power calculations of linear mixed effects models with random slope [68]. Based on the previous studies, we conducted separate sample size calculations for alcohol-related hospital admissions and reported crime rates. For both analyses we assumed a standard level of statistical significance α (5%) and statistical power β (80%), and further assumed a 9-year follow-up (2009–2018) and a two-sided alternative. Table 4 outlines the detectable effect size with 20 intervention and 20 control areas.

**Table 4 Tab4:** Sample size data

	Expected average effect size %/year (slope)	Between-slope variance	Residual variance model	Number of areas in each group
*From previous study of impact of licensing on alcohol-related crime* [29]				
Crime rates^a^	−4.00% (−0.04)	0.003	0.03	29
	−5.00% (−0.04)	0.003	0.03	19
	−6.00% (−0.06)	0.003	0.03	13
*From previous study of impact of licensing on alcohol-related hospital admissions* [28]				
Rates	−2.31% (−0.229)	0.110	0.011	34
*Current study - minimum detectable effect size with proposed sample size*				
20 areas per group	−3.00% (−0.296)	0.110	0.011	20

^a^Effect size is a range between 4 and 6% as estimated by d Vocht et al. (2016) using quadratic trends

Based on Table 4, we expect the study to be able to detect effects on our outcomes within the range found in previous observational studies with 20 intervention and 20 control areas.

Previous studies have not evaluated the impact of local licensing on attendances at Accident and Emergency (A&E) departments. Injuries and accidents are the largest single driver of A&E attendances [69] and are strongly linked to acute alcohol consumption and intoxication [70]. Therefore we expect an effect size in or around the range found for crimes as these are also strongly linked to acute alcohol consumption [71].

